**Figure figure1:**
[figure not shown]
Study flowchart. Patient data includes the following questionnaires: Pictorial Blood Assessment Chart (PBAC), Numeric Pain Rating Scale (NRS), Facet 1:Pain and discomfort WHOQOL-100, World Health Organization Quality Of Life-Bref (WHOQOL-Bref), Short Form-12 (SF-12), Facet 15: sexual activity domain WHOQOL-100, recovery (RI-10), Euro-QOL 5D (EQ-5D), patient preference (vignette), and patient satisfaction (Likert-scale).

### Safety Monitoring and Interim Analysis

Since both treatment options have proven their safety, no specific risks apply. This study is conducted to determine the efficacy of the treatment. However, safety monitoring without direct involvement in the trial (clinical research bureau, VUMC) will be installed to monitor the setup and conduct of the trial. No interim analysis is planned because of the relatively small sample size.

All serious adverse events (SAEs) will be reported to the accredited METC that approved the protocol, within 15 days after the sponsor has first knowledge of the serious adverse events. SAEs that result in death or are life threatening should be reported expedited. The expedited reporting will occur no later than 48 days after the responsible investigator has first knowledge of the adverse event. In case of more than one SAE, the METC will be notified. This committee can advise to terminate the trial due to safety reasons.

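### The expedited limit for fatal or life-threatening SAEs (48 days) is longer than the limit for all SAEs (15 days), so the two reporting rules contradict each other as written

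*Protocol article*

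**What the plan says.** All of the relevant text is in the protocol article, section Safety Monitoring and Interim Analysis.

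- General rule, scope and recipient: "All serious adverse events (SAEs) will be reported to the accredited METC that approved the protocol".
- General rule, limit: "within 15 days after the sponsor has first knowledge of the serious adverse events".
- Events singled out: "SAEs that result in death or are life threatening should be reported expedited".
- Limit for those events: "The expedited reporting will occur no later than 48 days after the responsible investigator has first knowledge of the adverse event".
- A further notification sentence: "In case of more than one SAE, the METC will be notified".
- The committee's role: "This committee can advise to terminate the trial due to safety reasons".

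The section also provides for monitoring of the trial's setup and conduct by a clinical research bureau that is not directly involved in the trial. On interim looks it says: "No interim analysis is planned because of the relatively small sample size". No other section of the article gives an SAE reporting limit.

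**The concern.** An expedited route exists to be quicker than the ordinary one. Here the ordinary route allows 15 days and the expedited route, reserved for deaths and life-threatening events, allows 48. The name and the number cannot both be right.

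What is at stake is safety oversight, not the statistical analysis. There is no interim analysis, and the METC is the only body that the section names as able to advise stopping for safety. Its use of that power depends on when reports reach it. The Results section says inclusion began in November 2015 and was expected to end in November 2019, so any reporting rule in force applies to women being treated.

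Two neighbouring points are unclear. The 15-day clock starts with the sponsor's knowledge and the 48-day clock with the investigator's. The sentence about more than one SAE sits awkwardly beside the commitment to report every SAE.

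**Working it through.** **Inputs, all from Safety Monitoring and Interim Analysis**

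- General limit: 15 days from the sponsor's first knowledge. It covers all SAEs, with no exception for fatal or life-threatening ones.
- Expedited limit: 48 days from the responsible investigator's first knowledge. It covers fatal or life-threatening SAEs.
- The expedited sentences name no recipient. From the context I take it to be the METC.

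**Step 1. Compare the limits at face value.** 48 − 15 = 33 days, and 48 / 15 = 3.2. The expedited limit is the longer one.

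**Step 2. Put both on one clock.** Let L be the number of days from investigator knowledge to sponsor knowledge. On the investigator's clock, the general limit falls on day 15 + L and the expedited limit on day 48. The expedited limit is the later one whenever 15 + L < 48, that is, L < 33. The article gives no value for L, so the values below are assumptions that show the range.

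| Assumed L (days) | General limit (15 + L) | Expedited limit | Expedited later by |
|---|---|---|---|
| 0 | day 15 | day 48 | 33 days |
| 1 | day 16 | day 48 | 32 days |
| 7 | day 22 | day 48 | 26 days |
| 14 | day 29 | day 48 | 19 days |
| 33 | day 48 | day 48 | 0 days |

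The order reverses only when L exceeds 33 days. The different clock starts therefore do not resolve the conflict, but they do make 33 days a maximum.

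**Step 3. Take the two possible readings.**

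- *Both rules bind.* A fatal event is an SAE, so it is already due at the METC within 15 days of sponsor knowledge. The 48-day limit then adds nothing unless L exceeds 33 days.
- *The expedited sentence is the specific rule and displaces the general one.* A fatal or life-threatening event may then arrive as late as day 48 on the investigator's clock, while another SAE is due on day 15 + L. The gravest events may arrive up to 33 days later than the rest.

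Neither reading gives an expedited route that does its job.

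**Step 4. The neighbouring sentences.** Different clock starts for two routes are not in themselves a contradiction. The sentence about more than one SAE can be read as an extra notice when events accumulate, or as a looser trigger. The text does not settle which.

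**The case against.** The strongest counter-argument is that the 15-day rule covers every SAE without exception. On the full text, a death is still due at the METC within 15 days of sponsor knowledge, and the 48-day sentence is idle rather than harmful. This stands as one reading. It limits what can be said about harm, but it leaves an expedited limit with no function.

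A reader might infer that a site could report a death after 48 days and still comply. The article does not support that. A report after day 48 breaches even the lenient rule. A report between the general limit and day 48 complies only if the expedited sentence replaces the general rule, which the text never says. The 15-day clock also runs from the sponsor's knowledge, not the site's.

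A reader might also infer that slower reporting of deaths was intended. The wording points the other way: the route is called expedited and is kept for the worst events, so a drafting slip is more likely than a design decision.

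The article condenses a fuller protocol approved by the ethics committee and the hospital boards. That protocol is not shown and may carry a different figure. This stands too: effects at the sites cannot be shown from the article. It does not excuse the article, which prints explicit limits that conflict rather than leaving the detail to the fuller document.

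Finally, oversight does not rest on the METC alone, because the clinical research bureau also monitors the trial. The section gives the bureau no role in advising termination, so timely reports to the METC still matter.

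**Conclusion.** The point holds as an internal contradiction in a stated safety-reporting rule, and the text is wrong as written. The size is 48 against 15 days. The gap of 33 days is a ceiling that assumes investigator and sponsor learn of the event on the same day, and it shrinks by one day for each day of lag. A later arrival of the gravest events follows only if the expedited sentence is read as the specific rule. If both rules bind, the defect is a redundant limit. Both readings assume that expedited reports go to the METC.

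The clock starts and the sentence about more than one SAE are ambiguities, not clear contradictions. Whether any site works to the 48-day figure is unknown.

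**What to change.** Check the 48-day figure against the METC-approved protocol and reconcile the two limits so that the expedited route is not slower than the ordinary one. Which number of days is right is for that protocol to settle, not this review.

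In the same correction:

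- state the recipient and the clock start for each route;
- say how the sentence about more than one SAE relates to the commitment to report all SAEs.

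Correct the published article. Notify the sites only if the operative protocol carries the same wording. The cost is a short text correction and, if needed, one notice. Nothing in the design or analysis changes.

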## Results

Inclusion of patients started in November 2015. The expected end date is November 2019. Data collection for the primary outcome will be expected to last until May 2020. Data collection concerning the secondary outcomes are expected two years following the last included patient. Analysis has not yet started as of this article’s submission.

## Discussion

### Summary

With this randomized controlled trial, we aim to evaluate the impact of UAE on HRQOL in a randomized comparison to hysterectomy in patients with symptomatic adenomyosis.

### Strengths and Limitations

This is the first randomized controlled trial evaluating effectiveness of UAE versus hysterectomy in patients with symptomatic adenomyosis. The QUESTA trial uses a web-based randomization program with the use of allocation concealment which reduces the chance of selection bias. The study is not blinded for the patient or health care worker which could possibly influence the outcomes. Blinding is impossible considering the nature of the treatments. Earlier studies reported on UAE being more cost-effective compared to hysterectomy, however these studies were conducted in patients with fibroids and mostly carried out through abdominal hysterectomies [31]. Over the years hysterectomy techniques have changed and the more cost-effective laparoscopy has become available. No studies have yet reported on cost effectiveness of UAE versus laparoscopic hysterectomy. We expect UAE to be more cost effective since the procedure itself is less expensive and recovery time is shorter [32], however we do expect consultation to be more frequent in the UAE group. We note that we allow all hysterectomy techniques in this study due to the intention to treat analysis. It will be registered and corrected for in analysis.

Disease specific questionnaires for adenomyosis have not yet been developed. Used questionnaires are validated in terms of quality of life, pain, heavy menstrual bleeding, sexual functioning, recovery, and allocation satisfaction and proved to be disease specific in the EMMY trial [13].

The follow-up in this trial is set at 24 months. This could be a limitation since 5- and 10-year follow-up of the EMMY trial showed additional hysterectomies in the UAE group [33,34]. Depending on the result of this trial a possibility to extend follow-up was included in the informed consent.

In the last 15 years, 30 cohorts and case series [15-26,35-52] described UAE in the treatment of symptomatic adenomoysis. The lack of level 1 evidence, heterogeneous particle use and UAE techniques make the development of a national guideline for standardized UAE in the treatment of adenomyosis challenging. We provide a mini-protocol on the usage of the standardized microspheres, however we do not provide a specific UAE technique protocol because we assume general UAE techniques will be followed [28]. In addition, we wish to maintain the intention to treat analysis of the Dutch population treated in the UAE centers.

### Potential Impact and Implications

Results of the QUESTA trial will provide knowledge for the most optimal treatment regimen in terms of HRQOL, side-effects, complications and satisfaction with allocated treatment. Hysterectomy requires hospitalization of 2 to 4 days, depending on the approach [31]. On the other hand, the source of adenomyosis is removed and might provide a more definite solution. An embolization is less invasive and in general, requires hospitalization of only 1 night [31]. Meanwhile, the uterus is preserved and complaints may continue (possibly to a lesser extent). How these pros and cons relate between the two strategies is unknown. If embolization proves to be comparable in terms of HRQOL, this can be offered to patients as a less invasive alternative, in particular in women that would like to preserve the uterus. These study outcomes could inform future patients about the expected effect of UAE and hysterectomy in the treatment of symptomatic adenomyosis and could therefore support shared decision making. These results are expected to improve patients’ wellbeing and quality of life.

## Appendix

Multimedia Appendix 1 Text and animations on the website.

## Abbreviations

AMH: Anti-Mullerian hormone
eCRF: electronic clinical report forms
EMMY: Embolization versus Hysterectomy
HRQOL: Health-Related Quality of Life
MRI: magnetic resonsnce imaging
PMMA: polymethylmethacrylate
QUESTA: Quality of Life after Embolization vs Hysterectomy in Adenomyosis
SF-12: Short Form-12
TLH: total laparoscopic hysterectomy
TVUS: transvaginal ultrasound
UAE: uterine artery embolization
VH: vaginal hysterectomy
WHOQOL-bref: World Health Organization Quality Of Life-Bref
